**Trial Protocol**

**Synopsis**

We propose a randomized controlled, non-inferiority trial to evaluate the effectiveness of two HIV testing strategies among 278 pregnant women seeking prenatal care at San Francisco General Hospital. The two strategies will include pretest/post-test counseling using prenatal care nurses and medical providers (control arm; current standard of care at San Francisco General Hospital [SFGH]) and an abbreviated pretest/post-test CDC recommended strategy using prenatal care nurses and medical providers (study arm). We hypothesize that the abbreviated CDC recommended strategy will be equally acceptable to patients as the standard strategy currently used. Eligible participants will include Spanish or English-speaking women seeking prenatal care at San Francisco General Hospital over the course of approximately one year. Eligible women presenting to SFGH physician or midwife prenatal clinics will be recruited, consented and randomized by study staff to either the standard or abbreviated testing strategy. The outcomes studied will be patient satisfaction and the proportion of study participants who undergo HIV testing. Satisfaction will be measured using the validated Decisional Conflict scale.

**Specific Aims**

1. To compare the acceptability of standard and abbreviated HIV counseling/testing strategies among a sample of low- income, urban, ethnically diverse prenatal patients.
2. To create an abbreviated HIV counseling/testing protocol compatible with the new California prenatal HIV testing law (AB 1676) that can be used in prenatal settings throughout the state.
3. To compare the proportion of enrolled pregnant women tested for HIV by the standard, risk-based vs. abbreviated counseling/testing strategy.
4. To compare the proportion of HIV-tested pregnant women receiving their HIV test results by the standard vs. abbreviated counseling/testing strategy.

**Background and Significance**

Approximately 40% of HIV-infected infants in the United States in 2000 were born to women not diagnosed with their HIV prior to delivery. (1) There are now effective medical therapies to prevent perinatal transmission, including anti-retroviral therapy, but this requires diagnoses of maternal HIV prior to delivery. Both the Centers for Disease Control and Prevention (CDC) and Institute of Medicine (IOM) have published strong recommendations for universal HIV-antibody testing of pregnant women. (8-12) There are currently two common testing strategies; in an opt-out approach, women are informed of the inclusion of HIV testing in the standard battery of prenatal labs and may decline such testing, whereas opt-in strategies use more traditional voluntary HIV counseling and testing techniques, with a specific informed-consent process. In a recent CDC retrospective analysis, prenatal HIV testing frequencies differed widely according to testing strategy throughout the United States and Canada. (16) Prenatal HIV testing was most common in areas with an opt-out approach, up to 98%, whereas regions using an opt-in approach had testing frequencies as low as 25%. While there are population-based studies such as this one and other observational studies using historical controls (18) supporting opt-out testing, there have been no randomized trials directly comparing opt-in and opt-out strategies. In addition, studies have shown that provider-performed HIV counseling and testing increases uptake of HIV testing in the perinatal setting, and is equally acceptable as testing strategies involving passive HIV testing education. (20)

The California legislature and former Governor Gray Davis passed Assembly Bill (AB) 1676, which requires all prenatal providers to inform their patients of their intent to include HIV testing as part of the routine battery of prenatal labs (similar to opt-out) but also requires pre-test counseling and written informed consent (similar to opt-in). Thus while opt-out HIV testing is restricted in California, an abbreviated provider-performed HIV counseling and testing strategy would be possible.

**Preliminary Studies**

A retrospective chart review of pregnant women accessing prenatal care at SFGH Women’s Health Clinic (WHC) showed that due to the change in standard of care at SFGH, from a dedicated HIV counseling and testing service to provider-performed counseling and testing, prenatal HIV testing uptake at SFGH has increased from 52% in 2003 to 93% as of April 2006. In a cross-sectional study of prenatal patients at SFGH WHC, nearly 70% of women surveyed supported routine testing as compared to 27% who supported elective testing. This support for routine prenatal HIV testing was comparable to these women’s attitudes towards routine rubella screening (63% support) and routine gonorrhea/chlamydia screening (77% support). The study we propose would be the natural next step in more specifically evaluating the routinization and streamlining of HIV testing in the prenatal care setting through the use of a rigorous randomized methodology.

**Study Design**

This will be a randomized controlled, non-inferiority trial comparing two HIV testing strategies among English and Spanish-speaking patients presenting for prenatal care at SFGH WHC over the course of approximately one year. Eligible participants will be randomized by study personnel to either standard HIV counseling and testing (control arm) or abbreviated counseling and testing (study arm). See Appendix 1. Participants will receive a standard prenatal HIV testing brochure, undergo one of two HIV counseling/testing strategies, submit blood for an HIV-1 antibody test, and will follow-up with their medical provider for HIV test results. Upon completion of counseling, participants will undergo a short, structured (Pre-test) questionnaire administered by study staff. Following testing and receipt of results, participants will complete a second (Post-test) structured questionnaire administered by study staff. Eligible women presenting to SFGH physician or midwife prenatal clinics will be recruited, consented and randomized by study staff to either the standard or abbreviated testing strategy. The outcomes studied will be patient satisfaction and the proportion of study participants who undergo HIV testing. Potential confounder variables to be measured will include demographic characteristics, prior HIV testing history, knowledge about HIV/AIDS, attitudes towards HIV testing, HIV test result, and type of provider (physician versus midwife).

All procedures will take place in SFGH Women’s Health Clinic. Time required of the subjects outside of routine prenatal care visits includes approximately 10 minutes for recruitment and randomization, 5-10 minutes for the pre-test questionnaire, and 5 minutes for the post-test questionnaire. If the patient is lost to follow-up and can no longer be reached upon visiting the clinic, the follow-up interview will be attempted to be conducted via telephone. We will specifically ask the participant permission on whether or not we can leave a simple message on her voicemail if she is lost to follow-up.

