**Recruitment**

All English and Spanish-speaking pregnant patients initiating prenatal care at SFGH Women’s Health Center are eligible to participate. We will offer study enrollment to English and Spanish speaking pregnant patients initiating prenatal care at SFGH WHC. We will include women who are 16 years or older and are capable of providing informed consent. We will exclude women who do not speak either English or Spanish, women who are not able to give informed consent, women younger than 16 years old and women who obtained an HIV test during the index pregnancy prior to initiation of prenatal care at SFGH. In addition, we will exclude pregnant women who are known to be infected with HIV at initiation of prenatal care at SFGH.

We will be posting flyers in the Women’s Health Clinic so that patients will be aware of the study. We will also be providing only a small monetary incentive for their participation. We will reimburse the subjects $10 for their participation in the study if such funding is available at the time of subject recruitment. Specifically, we will reimburse $5 at the completion of the pre-test questionnaire and $5 at the completion of the post-test questionnaire. Additionally, bilingual/bicultural research staff will be conducting recruitment, administering the study consents and surveys. We will also be using a validated low-literacy scale to measure satisfaction.

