**Sample Size**

Our sample size calculation was based on the primary outcome, decisional conflict score. Because this was a non-inferiority trial, the trial was designed to be able to exclude an actual difference between the abbreviated and standard counseling arms of greater than 5.625 (the non-inferiority margin) with respect to the mean decisional conflict score (DCS) in each group. To calculate our sample size, we used a type-I error rate (alpha) of 0.05 with an 80% power, a common standard deviation of 18.75 for the DCS, and a one-sided two group t-test of equivalence in means (equal n's) to arrive at 139 patients in each arm for a total of 278 participants. 20, 21 Assuming 75% participation as was seen in a 1997 study of the same patient population (i.e. those accepting enrollment and randomization), we will need to approach 371 women overall.

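### One research-staff group both randomises the women and administers the questionnaires, with no stated step that keeps interviewers unaware of the arm, although the primary outcome is a subjective score

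*Protocol*

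**What the plan says.** The protocol's Study Design section states that eligible women are "recruited, consented and randomized by study staff to either the standard or abbreviated testing strategy". The Synopsis says the same, and an earlier sentence of Study Design also gives randomisation to study personnel.

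Once counselling is finished, "participants will undergo a short, structured (Pre-test) questionnaire administered by study staff". A second structured questionnaire, after results are received, is also given by study staff, with a telephone attempt for women who can no longer be reached in clinic. The Recruitment section ties the roles together: "bilingual/bicultural research staff will be conducting recruitment, administering the study consents and surveys".

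The Sample Size section identifies the outcome at stake: "Our sample size calculation was based on the primary outcome, decisional conflict score".

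Two further facts matter for the remedy. According to the Synopsis, prenatal nurses and medical providers, not research staff, deliver the counselling in both arms. According to Informed Consent, consent is taken at the nursing intake visit.

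The text shown does not mention interviewer blinding, separation of the randomising and interviewing roles, allocation concealment or self-completion of the scale.

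**The concern.** A staff group that assigns the arm and then reads out and records answers to a subjective scale can influence the score through tone, prompting or the handling of unclear answers. The Synopsis states the hypothesis that the two strategies are equally acceptable. In a superiority trial, an interviewer who expects similar scores works against the hypothesis. In a non-inferiority trial, the same expectation works towards success. The influence could also run the other way, for example if an interviewer thinks the shorter session leaves women less well prepared, and the trial would then lose power. The planned intention-to-treat analysis does not correct either effect, because it governs who is analysed in which arm and not how the score was obtained.

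This is not a detail normally left to a statistical analysis plan. Who randomises and who interviews is trial conduct, and the protocol assigns both tasks explicitly.

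**Working it through.** **Inputs (all from Sample Size).** Margin 5.625 points; "a common standard deviation of 18.75 for the DCS"; "a type-I error rate (alpha) of 0.05 with an 80% power"; "a one-sided two group t-test of equivalence in means"; 139 women per arm.

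**Step 1: reproduce the plan's figure.** With no true difference, the normal approximation gives

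n = 2 × (1.645 + 0.842)² × 18.75² / 5.625² ≈ 137.4, so 138 per arm.

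With the noncentral t distribution, power is 79.98% at 138 and 80.23% at 139. The stated 139 per arm (278 in total) is therefore right for a t-test.

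**Step 2: standard error of the difference.**

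SE = 18.75 × √(2/139) = 2.249 points.

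**Step 3: effect of an interviewer shift.** The documents give no size for such a shift, so *b* = 1, 2 and 3 points are assumptions. One point is 1/18.75 = 0.05 SD and 1/5.625 = 18% of the margin. By the normal approximation:

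- False non-inferiority when the true difference equals the margin and the shift favours the abbreviated arm: Φ(*b*/2.249 − 1.645).
- Power when the true difference is zero and the shift goes against the abbreviated arm: Φ((5.625 − *b*)/2.249 − 1.645).

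| Assumed shift *b* | False non-inferiority at the margin (shift favours abbreviated arm) | Power at no true difference (shift against abbreviated arm) |
|---|---|---|
| 0 | 0.050 | 0.804 |
| 1 point | 0.115 | 0.660 |
| 2 points | 0.225 | 0.487 |
| 3 points | 0.378 | 0.316 |

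Example for 1 point: Φ(0.445 − 1.645) = Φ(−1.200) = 0.115, and Φ(4.625/2.249 − 1.645) = Φ(0.411) = 0.660. A t-test with 276 degrees of freedom gives the same false non-inferiority rates to within 0.001.

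**Step 4: shrinkage instead of a fixed shift.** If interviewers tend to elicit similar answers in both arms, the true difference is scaled down. A 20% shrinkage at the margin removes 0.20 × 5.625 = 1.125 points, and Φ(1.125/2.249 − 1.645) = 0.126. The 20% is also an assumption.

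**The case against.** Several counter-arguments have force.

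- **Same person, and unblinded collection.** A reader might infer that the individual who randomises a woman also interviews her, and that the score is collected unblinded. The documents do not establish either. They name staff categories, not individuals; the second interview comes later and may be by telephone; and Appendix 1, cited in Study Design, is not in the text at hand. The text supports only that one staff group holds both roles and that no safeguard is stated. Nor does it say which questionnaire carries the decisional conflict items, but study staff give both, so the point holds either way.
- **Mitigations.** The questionnaires are structured and the satisfaction scale is described as validated and low-literacy. That narrows interviewer discretion without removing it. Administration by bilingual staff is a defensible choice for this population, and the remedy leaves it in place.
- **Assumed sizes and direction.** The shifts are hypothetical, and no passage shows that they would favour the abbreviated arm. This stands, which is why both directions are shown.
- **Limits of the remedy.** It is tempting to say that moving the opening of the allocation would blind the interviewers. That is too strong. The first questionnaire follows counselling in the same clinic, one arm is shorter by design, and women may describe what they received. The woman supplies the score and cannot be blinded to her own counselling.

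**Conclusion.** The point holds as an avoidable exposure to bias in the primary outcome. The protocol gives allocation and interviewing to one research-staff group and states nothing that keeps interviewers unaware of the arm. The documents do not show that bias would occur, which way it would go or how large it would be.

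The arithmetic shows how little would be enough. Because the standard error is 2.249 points, an assumed shift of 1 to 2 points (18% to 36% of the margin) raises false non-inferiority at the margin from 5% to about 11.5% to 22%, or lowers power at no true difference from about 80% to 66% to 49%. These figures rest on the protocol's SD and sample size, a constant shift and complete outcome data. The sample size itself is correct and is not in question. This is a low-cost improvement and does not mean the design is invalid.

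**What to change.** Amend the randomisation wording in three places so that they agree: the Synopsis sentence and both Study Design sentences that give randomisation to study personnel or staff. State that:

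- after consent, study staff hand a sequentially numbered, sealed opaque envelope to the nurse or provider who will do the counselling;
- that clinician opens it, delivers the assigned strategy, and passes the assignment to the other clinicians counselling that woman;
- study staff who administer the questionnaires are not told the arm, ask women not to describe their counselling, and ask the decisional conflict items first.

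Changing only one of the three sentences would leave the protocol contradicting itself on who randomises.

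The cost is a brief task for clinic staff. The counselling clinicians must know the arm in any case, and consent already takes place at the nursing intake visit, so no extra staff category, visit or participant is needed and the sample size stays at 139 per arm. The envelope also adds an allocation-concealment step that the text shown does not describe. Blinding will remain incomplete, because women's remarks or session length may reveal the arm.

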**Statistical Analysis**

We will measure the receipt of results as a proportion of those undergoing testing who receive their results before the onset of labor. We will compare the proportions between the 2 groups using the χ² test. We will calculate a satisfaction score for all study participants using the Decisional Conflict Scale which has been validated in many study populations. (20) We will compare mean satisfaction scores between the 2 groups using the Student t-test (if the distribution is parametric) or Wilcox rank-sum test (if the distribution is non-parametric). Lastly, we will conduct multivariate logistic regression to assess independent predictors using STATA SE8. We will test for interaction and stratify the multivariate analysis accordingly. We will conduct a strict intention-to-treat analysis. We will develop the data collection forms with the date and alphanumeric code on each page. Each variable will be named and coded. We will utilize a Microsoft ACCESS relational database. We will pretest the data management system with “dummy” data. We will promptly enter the data after collection and set criteria within the ACCESS database to minimize the likelihood of incorrect data entry. Once all data is entered, we will edit the database, checking for missing data, illogical data and outliers. We will log any changes made in the database during the editing process and freeze the final database before importing the data into statistical analysis software. We will then analyze and archive the database.

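### HIV test result, and apparently HIV knowledge and testing attitudes, are listed as potential confounders although they arise after randomisation; they should not be adjusted for in any model of the arm effect

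*Protocol*

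**What the plan says.** The protocol's Study Design section states: "Potential confounder variables to be measured will include demographic characteristics, prior HIV testing history, knowledge about HIV/AIDS, attitudes towards HIV testing, HIV test result". The sentence ends by adding type of provider.

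The same section sets the timing of data collection. The first questionnaire follows the intervention: "Upon completion of counseling, participants will undergo a short, structured (Pre-test) questionnaire administered by study staff". The second comes later still: "Following testing and receipt of results, participants will complete a second (Post-test) structured questionnaire administered by study staff". The time asked of participants outside routine visits is "approximately 10 minutes for recruitment and randomization, 5-10 minutes for the pre-test questionnaire, and 5 minutes for the post-test questionnaire". No questionnaire before randomisation is listed.

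Under Statistical Analysis, the DCS comparison is unadjusted: "We will compare mean satisfaction scores between the 2 groups using the Student t-test", with a rank-sum test as the alternative. One multivariable analysis follows: "Lastly, we will conduct multivariate logistic regression to assess independent predictors using STATA SE8". Interaction tests and stratification are to be added, and the analysis is declared to be strictly by intention to treat. Sample Size names the primary endpoint: "Our sample size calculation was based on the primary outcome, decisional conflict score".

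**The concern.** In a randomised comparison, a covariate used for adjustment should be fixed before allocation. A variable that the intervention can change is a possible mediator. Conditioning on it removes whatever part of the arm effect passes through it, and can also introduce bias through unmeasured causes that it shares with the outcome. Counselling can plausibly change knowledge about HIV and attitudes to testing.

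HIV test result raises a second problem. It is undefined for women who decline testing, and testing uptake is itself a trial outcome. A model that includes it is restricted to women selected by something that happened after randomisation.

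What is at stake is the meaning of the arm coefficient in any adjusted model, and which women that model retains.

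**Working it through.** **1. Does the list touch the primary comparison?** Inputs from Sample Size: margin 5.625, SD 18.75, one-sided alpha 0.05, power 80%, equal arms, 139 per arm.

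- Normal approximation: n = 2 × (18.75/5.625)² × (1.645 + 0.842)² = 2 × 11.11 × 6.18 ≈ 137.4, so 138 per arm.
- Exact noncentral t: 139 per arm, power 80.2%.

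The stated figure is reproduced by an unadjusted two-group t-test. The planned DCS comparison is also unadjusted, so the covariate list enters neither.

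**2. When is each listed variable determined?**

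| Variable | Timing from the protocol | Status |
|---|---|---|
| Demographics, prior HIV testing | Facts that precede enrolment | Before randomisation |
| Type of provider | Physician or midwife; time of assignment not stated | Before randomisation only if already set |
| HIV knowledge, testing attitudes | Collecting form not named; both questionnaires follow counselling and no baseline form is listed | After the intervention, by inference |
| HIV test result | Recruitment excludes women already tested in this pregnancy before starting care at the hospital, and women known to be infected | After randomisation, with certainty |

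The label of the first questionnaire refers to the blood test. It does not mean before counselling.

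**3. What does test result do in a model?**

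- *Testing uptake as outcome.* Every woman with a result was tested. A complete-case fit therefore has a constant outcome and cannot be estimated. Coding the untested as a separate category does not help, because that category predicts the outcome perfectly.
- *An outcome defined for all women.* A complete-case fit loses all untested women, so it is no longer by intention to treat.
- *Receipt of results as outcome.* The denominator is already women who were tested, so no one is lost for being untested.

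**4. Is the direction of bias known?** The document gives no effect of arm on knowledge or attitudes and no effect of those on DCS, so the following values are assumptions. The check uses a linear DCS model, which the protocol does not plan, only to see whether the sign is determined. Settings: 139 per arm, SD 18.75, true arm difference equal to the margin (higher score counted as worse), 5,000 simulated trials per row. For a mediator, the adjusted estimate targets 5.625 − (slope × shift), where shift is the arm effect on the covariate in SD units and slope is DCS points per SD.

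| Shift | Slope | Target | Simulated adjusted estimate | Non-inferiority claimed |
|---|---|---|---|---|
| −0.2 | −5 | 4.625 | 4.63 | 11.8% |
| −0.3 | −5.625 | 3.94 | 3.96 | 18.7% |
| −0.5 | −5.625 | 2.81 | 2.81 | 35.3% |
| +0.3 | −5.625 | 7.31 | 7.29 | 0.9% |
| 0 | −5.625 | 5.625 | 5.64 | 4.8% |

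If the covariate has no effect on DCS (shift −0.3, slope 0) but shares an unmeasured cause with it, the estimate was 6.10 (claims 2.9%) or 5.13 (claims 7.4%), depending on the sign of that association. Without the covariate, the estimate was 5.61 to 5.65 and claims were 4.6% to 5.5% throughout.

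The distortion can go either way, and it vanishes when the arm does not affect the covariate.

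**The case against.** The strongest reply is that the protocol states no adjustment set. Study Design calls these variables potential confounders to be measured. Statistical Analysis ties the regression to independent predictors, without naming its outcome or covariates and without saying that an adjusted arm effect will be reported. Knowledge and attitudes are legitimate candidates in a descriptive model of who accepts testing. Covariate choice for a secondary model is commonly left to the SAP, which is not shown. The form that collects knowledge and attitudes is not named either.

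Most of this stands, and it confines the point to a conditional one about a secondary model. Two things remain. The protocol does more than leave covariates open: it classes these variables as confounders, and for HIV test result that is wrong on any reading. Nor can a later SAP fully repair the matter. It can drop the covariates, but it cannot recover baseline knowledge or attitudes that were never collected.

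A reader might go further and infer that adjustment would pull the arms together and so favour the abbreviated strategy on the non-inferiority test. The document does not support this. The non-inferiority comparison is unadjusted, the only multivariable model is logistic, and the inference needs the abbreviated arm to do harm through poorer knowledge or attitudes, which nothing in the protocol establishes. A reader might also infer that intention-to-treat is already breached. It is not: a breach would follow only if test result were actually entered in a model meant to cover all randomised women.

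**Conclusion.** The point holds as a misclassification written into the protocol, with consequences limited to any adjusted arm-effect model.

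- **Primary analysis:** no effect. The DCS comparison and the 139 per arm stand.
- **Secondary logistic regression:** if the listed variables are used as covariates, the arm coefficient does not estimate the total randomised effect. Size and direction are unknown. In the illustration, with a true 5% error rate, the rate of false claims ran from 0.9% to 35% according to the assumed signs and sizes. That range shows only that the direction is undetermined; it is not a forecast for this trial.
- **HIV test result:** entering it makes an uptake model unfittable and drops untested women from other models covering all participants. The number lost cannot be stated, because the protocol gives no expected uptake for the trial arms; the chart-review figure describes past clinic practice.

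That test result is post-randomisation is certain. The same status for knowledge and attitudes is a strong inference from the described schedule. The consequences assume that the list guides the regression, which the protocol neither states nor rules out.

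**What to change.** 1. State that, in any model estimating an arm effect, covariates are limited to variables fixed before randomisation: demographics, language, prior HIV testing, and type of provider if it is set before randomisation.
2. Remove HIV test result from the list of potential confounders and report it descriptively.
3. Treat knowledge and attitudes measured after counselling as outcomes or mediators. If adjustment for them is wanted, collect them before randomisation, for example at the recruitment contact.
4. If the regression is meant only to describe predictors, say so, and state that its arm coefficient will not be read as the effect of the strategy.

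The cost is a sentence or two of protocol text and, if the third item is taken up, moving some questions earlier. Asking them before counselling may prime participants slightly, but equally in both arms. The sample size does not change. The question order has to be settled before enrolment, since it cannot be corrected afterwards.
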